#### Study duration and schedule

The overall duration of this study is 4.5 years comprising a recruitment period of 2.5 years and a 2-year follow-up period for each patient enrolled. Clinical and economic data are recorded over the 2 year follow-up period.

#### Sample size

The sample size was calculated using the approach proposed by Frison and Pocock [19]. The calculation is based on the comparison between the two study arms of the mean of 4 post-treatment measurements during the 1st year of follow-up (at 3, 6, 9 and 12 months). Assuming a standard deviation of 2 points of HbA1c, a correlation of 0.4 between the pre- and post-randomization measurements, and a correlation of 0.5 between the post-randomization measurements, 117 patients are required per arm (234 patients in all) to detect a difference of 0.5 points of HbA1c with a power of 80%, a two-sided type I error of 5%. This calculation was computed using Stata SE 11.2 software. To avoid any loss of power due to patients lost to follow-up, the cohort obtained is increased by 20% to give a total of 282 patients to be enrolled (141 per arm).

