#### Outcomes

The primary endpoint is the difference between HbA1c level after 1 year of follow-up and the targeted HbA1c level defined at baseline by the physician in charge of the patient (based on the recommended strategy for glycemic control in type 2 diabetes) [17, 18]. HbA1c levels are measured by high-performance liquid chromatographic (HPLC) methods HbA1c levels will be measured at baseline, 3, 6, 9 and 12 months of follow-up.

The secondary outcomes are:

Comparison between the two arms for assessment at baseline and after 1 year of follow-up of:Improvement of nutritional knowledge, questionnaires will be given to patients.Dietary intake measured by a validated food survey based on 3-day food record.Physical activity practice, measured by the general physical activity questionnaire (GPAQ.Body composition, BMI (body mass index), waist circumference will be measured.Mean of blood glycaemia, self-monitoring blood glucose books will be copied.Total cholesterol, triglycerides and high density lipoprotein (HDL) cholesterol blood levels, a blood sample will be collected.Quality of life of patients, measured by the diabetes quality of life questionnaire (DQOL) and the EQ-5D questionnaires.

Direct and indirect costs will be recorded at baseline, throughout the study and at the closure visit. The economic analysis will be carried out from the cost payer’s point of view, Assurance Maladie (Health Insurance). Direct medical costs (directly attributable to patient treatment), direct costs of a non-medical nature (travelling expenses and the costs incurred through implementing the telemonitoring programme) and indirect costs (production losses) to be paid by health insurance, mutual insurance and patients will be calculated.

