##### Primary outcome analysis

The primary outcome (difference between HbA1c level after 1 year of follow-up and baseline targeted HbA1c level) will be compared between the two groups. The difference between the the intervention and control groups will be assessed firstly using bivariate analysis (Student’s T test), and secondly using mixed model analysis for repeated measures. The mixed model will be adjusted for the baseline value of HbA1c, as well as additional baseline variables that might be potential confounders: center, age, gender, treatment by insulin, duration of diabetes and history of diabetes complications. To manage missing data, a sensitivity analysis using the last observation carried forward (LOCF) technique will be applied. Secondary outcomes will be analyzed according to the same principles. A bivariate analysis will be computed, followed by a multivariate analysis of covariance (ANCOVA) adjusted for the baseline value of the corresponding secondary outcome and the same set of potential baseline confounders than in the primary outcome analysis.

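### The sample size is calculated for the baseline-adjusted mean of four HbA1c values, but the primary endpoint is the single 1-year value, for which the plan's own inputs give about 48–55% power, not 80%

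*Protocol article*

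**What the plan says.** Three sections of the protocol article bear on this.

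- **Sample size.** "The sample size was calculated using the approach proposed by Frison and Pocock". The quantity compared is the "comparison between the two study arms of the mean of 4 post-treatment measurements during the 1st year of follow-up"; those four visits fall at 3, 6, 9 and 12 months. The SD input reads "Assuming a standard deviation of 2 points of HbA1c". For pairs of one baseline and one follow-up value the plan takes "a correlation of 0.4 between the pre- and post-randomization measurements"; for pairs of follow-up values it takes "a correlation of 0.5 between the post-randomization measurements". The result is 117 patients per arm "to detect a difference of 0.5 points of HbA1c" with 80% power at a two-sided 5% level. A 20% increase for loss to follow-up gives 141 per arm.
- **Outcomes.** The definition reads: "The primary endpoint is the difference between HbA1c level after 1 year of follow-up and the targeted HbA1c level defined at baseline"; the treating physician sets that target. HbA1c is measured at baseline, 3, 6, 9 and 12 months.
- **Primary outcome analysis.** This section repeats the definition: "The primary outcome (difference between HbA1c level after 1 year of follow-up and baseline targeted HbA1c level) will be compared between the two groups". Testing is done first with Student's t-test, then with a mixed model for repeated measures. The mixed model adjusts for baseline HbA1c, center, age, gender, insulin treatment, diabetes duration and history of complications.

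The Abstract and Study objectives sections also state the aim in terms of HbA1c after 1 year of follow-up. No section makes the four-visit mean the primary endpoint, and none says which contrast the mixed model is to report.

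**The concern.** Averaging four correlated measurements and adjusting for baseline both reduce the variance of the treatment comparison. The sample size takes credit for both. The stated endpoint has no averaging, because it is one value at 1 year. The first-named test has neither averaging nor baseline adjustment. The 80% power is therefore attached to a comparison that the plan does not call primary.

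Two things are at stake. A non-significant 1-year result would be read as coming from a trial with 80% power to detect 0.5 points when, on the plan's assumptions, that chance was about one half. And because the mixed-model contrast is not named, the 12-month effect and the year-average effect both remain open as the primary result.

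**Working it through.** **Inputs** (Sample size section): SD of one HbA1c value 2, so variance 4; pre–post correlation 0.4; post–post correlation 0.5; difference 0.5; two-sided 5%; power 80%. The allocation is 1:1 (Allocation section).

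**Formulas.** With one baseline and *r* post-randomization values, the Frison–Pocock variances are:

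- post values only: 4 × (1 + (r − 1) × 0.5)/r
- change from baseline: 4 × [(1 + (r − 1) × 0.5)/r + 1 − 2 × 0.4]
- baseline-adjusted (ANCOVA): 4 × [(1 + (r − 1) × 0.5)/r − 0.4²]

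Patients per arm = 2 × (1.96 + 0.8416)² × variance / 0.5², where (1.96 + 0.8416)² = 7.849.

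**Step 1: reproduce 117.** For r = 4, the averaging factor is (1 + 3 × 0.5)/4 = 0.625.

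| Analysis of the four-visit mean | Variance | Patients per arm |
|---|---|---|
| ANCOVA | 4 × (0.625 − 0.16) = 1.86 | 116.8, so 117 |
| Post values only | 4 × 0.625 = 2.50 | 157 |
| Change from baseline | 4 × (0.625 + 0.2) = 3.30 | 207.2, so 208 |

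Only the ANCOVA version gives 117, with power 80.1%. Then 117 × 1.2 = 140.4, rounded up to the stated 141. The plan's arithmetic is right for the quantity it was applied to.

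**Step 2: apply the same inputs to the stated endpoint.** For r = 1 the averaging factor is 1. The variance is 4 for the unadjusted t-test and 4 × (1 − 0.16) = 3.36 with baseline adjustment. The latter is also, approximately, the variance for the 12-month contrast of the mixed model when data are complete.

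The standard error of the difference is √(2 × variance / n). At n = 117 it is 0.178 for the four-visit ANCOVA, 0.240 for the 12-month ANCOVA and 0.261 for the 12-month t-test. Dividing 0.5 by these gives about 2.80, 2.09 and 1.91, to be set against the critical value 1.96.

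| Comparison | Power, 117 per arm | Power, 141 per arm | Difference detectable with 80% power, 117 per arm | Evaluable per arm for 80% power |
|---|---|---|---|---|
| Mean of four, baseline-adjusted | 80.1% | 86.8% | 0.50 | 117 |
| 12 months, baseline-adjusted | 55.0% | 62.9% | 0.67 | 211 |
| 12 months, t-test | 48.1% | 55.5% | 0.73 | 252 |

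The noncentral t distribution changes little: 47.8% for the t-test and 54.7% for the adjusted analysis at 117 per arm.

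**Step 3: allow for the target.** The endpoint subtracts a patient-specific target. If the target were the same for everyone, the SD would stay at 2. The protocol gives no SD for the target, so a range has to be assumed. With a target SD of 0 to 1 point and a correlation of 0 to 0.4 with the 1-year value, the SD of the difference runs from about 1.83 to 2.24. T-test power at 117 per arm is then about 40–55%.

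**The case against.** The strongest objection is that the planned mixed model uses all four visits and adjusts for baseline. If its arm effect is taken as common to the four visits, it has about 80% power and matches the sample size. Nothing says that the t-test governs the conclusion, and choosing the contrast is commonly left to an analysis plan. This stands in part: the 48% figure matters only if the t-test decides the trial. But an effect averaged over the year does not estimate the 1-year endpoint that the protocol defines twice. A 12-month contrast does, and has about 55% power. The model can match the endpoint or the sample size, not both. The contradiction lies in what the protocol states, not in a detail it leaves out.

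A second objection is that SD 2 looks large. Entry is limited to HbA1c above 6.5 and up to 10%, a range of 3.5 points, so the baseline SD cannot exceed 1.75. Follow-up values are not bounded in this way, and no observed SD is given. If the true SD were smaller, 1-year power at 117 per arm would be higher: 72% (t-test) or 79% (adjusted) at SD 1.5, and 81% or 87% at SD 1.35. An SD of about 1.37 (t-test) or 1.49 (adjusted) would be needed for 80%. This is a fair limit on the finding: 48–55% is power under the plan's stated inputs, not a claim about the trial's true power. The protocol states SD 2, however, and does not argue for a smaller one.

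Third, the additional covariates in the mixed model could explain further variance and raise power above 55%. That is true, but the protocol gives no figure for it and the sample size takes no credit for it.

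Finally, a repeated-measures model can be fitted to the visit values, or to each value minus target, and the 12-month effect read from it. That is correct. The difficulty is only that a single 1-year difference is not itself a repeated outcome, so the contrast has to be named.

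**Conclusion.** The concern holds. The arithmetic behind 117 per arm is correct, but it is for the baseline-adjusted mean of four values, and the primary endpoint is one value at 1 year. Under SD 2, correlations 0.4 and 0.5, a difference of 0.5 and 117 evaluable per arm, the shortfall is about 25 percentage points with baseline adjustment (80.1 − 55.0) and 32 with the t-test (80.1 − 48.1).

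Using up the whole allowance for loss to follow-up does not close the gap. Variation in the target, over the range assumed above, does not change the conclusion. A materially smaller SD would reduce the shortfall or remove it, but that is not what the plan assumes. As written, the stated power does not belong to the stated primary comparison, and this must be corrected.

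**What to change.** Name the one analysis that decides the trial and give the power for it. There are two workable forms.

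- **(a) Keep the 1-year endpoint.** State that the decisive result is the 12-month contrast of the baseline-adjusted mixed model, with the t-test as supportive. Revise the Sample size section to say that 117 evaluable per arm gives about 55% power for 0.5 points and 80% power for 0.67 points. If the t-test is to decide, the figures are 48% and 0.73.
- **(b) Keep the sample size.** Define the primary contrast as the treatment effect averaged over 3, 6, 9 and 12 months, adjusted for baseline, and make the 12-month contrast the first secondary. Align the Abstract, Study objectives, Outcomes and Primary outcome analysis sections with this.

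Under either form, say how the target enters the repeated-measures model, for example as each visit's value minus the target. Make the choice before outcome data are examined by arm.

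The cost is wording only, since all four measurements are already scheduled. Form (a) discloses a less favourable power. Form (b) changes what is estimated, from the effect at 1 year to the average effect over the year. Neither delivers 80% power for 0.5 points at 1 year. On the plan's inputs, that would take 211 (adjusted) or 252 (t-test) evaluable patients per arm.

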#### Allocation

Randomization was based on a 1:1 ratio and stratified on the baseline HbA1c level (<7.5% vs ≥7.5%). The allocation sequence was randomly permuted in blocks of varying size (2, 4 or 6), generated by computer (Stata SE 11.2, ralloc procedure) by the methodologist. There was no blinding procedure in this open-label trial, however randomization was centralized at the Toulouse University Hospital and managed by the project manager and the two clinical research associates, and the allocation sequence was unknown to the investigators who enrolled participants.

#### Data collection method

Data are collected by the investigators, study staff and by patients called PROs (patient report outcomes) PROs. Hba1c levels, serum lipid profile, clinical exam and questionnaires were recorded on an e-crf (e-clinical report form) by single data entry.

Quarterly, the CRAs (clinical research associate) call the patients, over the 2-year period, to obtain protocol-related information: result of the HbA1c assay, medical treatments and adverse events.

Data obtained using biomedical sensors will be retained. Range checks were implemented to limit data entry mistakes on the e-crf. All the data obtained from the various sources (biomedical sensors, tablet, data entered by the clinicians, data entered by the CRA) will be merged into a single complete database. A simple input will be made on an input mask with logical controls for the clinical data. The data will be validated according to the data management plan defined jointly by the coordinating investigator and the epidemiology department (methodologist and statistician).

The data will be frozen after the last logical and coherence checks carried out at the beginning of the statistical analysis. Once all the CRFs have been entered and validated, and all the steps of the Data Management have been locked, the Data Manager can proceed to freeze the database, a certificate of which will be issued to the Project team.

The database will then be provided to the Statistician for analysis in accordance with the statistical analysis plan.

#### Statistical methods

##### Analysis population

Efficacy will be analyzed on an intent-to-treat (ITT) basis followed by a per protocol (PP) analysis, if required. The PP analysis will only be carried out if the ITT population differs from the PP population by more than 10%. A flow chart will be described and a detailed descriptive analysis of the distribution of baseline variables in the study population will be carried out per arm in order to check the randomization result (intervention/control) and globally.

##### Primary outcome analysis

The primary outcome (difference between HbA1c level after 1 year of follow-up and baseline targeted HbA1c level) will be compared between the two groups. The difference between the the intervention and control groups will be assessed firstly using bivariate analysis (Student’s T test), and secondly using mixed model analysis for repeated measures. The mixed model will be adjusted for the baseline value of HbA1c, as well as additional baseline variables that might be potential confounders: center, age, gender, treatment by insulin, duration of diabetes and history of diabetes complications. To manage missing data, a sensitivity analysis using the last observation carried forward (LOCF) technique will be applied. Secondary outcomes will be analyzed according to the same principles. A bivariate analysis will be computed, followed by a multivariate analysis of covariance (ANCOVA) adjusted for the baseline value of the corresponding secondary outcome and the same set of potential baseline confounders than in the primary outcome analysis.

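### The primary outcome gets two tests, neither named as decisive, and the one listed first is not the one the trial was sized for

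*Protocol article*

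**What the plan says.** Primary outcome analysis (Protocol article) has the arms compared on 1-year HbA1c minus the target set at baseline, "firstly using bivariate analysis (Student’s T test), and secondly using mixed model analysis for repeated measures". The mixed model is adjusted for baseline HbA1c, center and several patient characteristics; no adjustment is given for the t test. The section calls only the LOCF analysis a sensitivity analysis. It gives neither test a primary or supportive role, sets no testing order for claims, and does not state the model's treatment contrast.

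Sample size plans one comparison, of the mean of the values at months 3, 6, 9 and 12, with "a two-sided type I error of 5"%. Its inputs are:

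- "Assuming a standard deviation of 2 points of HbA1c"
- "a correlation of 0.4 between the pre- and post-randomization measurements"
- "a correlation of 0.5 between the post-randomization measurements"

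The target is "to detect a difference of 0.5 points of HbA1c with a power of 80"%. The result is 117 per arm, raised to 141.

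Allocation says that randomization was "stratified on the baseline HbA1c level (<7.5% vs ≥7.5"%).

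**The concern.** A confirmatory trial needs one analysis that answers the primary question, fixed before the results are known. Here two analyses are prescribed for one outcome and they differ in power. If they disagree, the article gives no rule for which one answers the primary objective. The trial is open-label, so a choice made after both p-values were visible would be hard to defend.

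The order adds to the problem. A reader who takes the first-listed test as the main one would rest the trial on an analysis that the sample-size section did not plan for.

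**Working it through.** **Inputs (Sample size section).** SD σ = 2; difference δ = 0.5; correlation of baseline with each follow-up value 0.4; correlation among follow-up values 0.5; four follow-up values; two-sided 5%; power 80%. (1.960 + 0.842)² = 7.849.

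**1. Reproduce the plan's figure.** For a baseline-adjusted comparison of the mean of four values, the Frison–Pocock variance factor is

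(1 + 3 × 0.5)/4 − 0.4² = 0.625 − 0.16 = 0.465.

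n per arm = 2 × σ² × factor × 7.849/δ² = 2 × 4 × 0.465 × 7.849/0.25 = 116.8, so 117. The stated figure is reproduced.

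**2. Try the other analyses with the same inputs.**

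| Analysis | Variance factor | n per arm for 80% | Power at 117 | Power at 141 |
|---|---|---|---|---|
| Baseline-adjusted, mean of four | 0.465 | 117 | 80% | 87% |
| t test, mean of four | 0.625 | 157 | 68% | 76% |
| Baseline-adjusted (simple ANCOVA), month 12 | 0.84 | 211 | 55% | 63% |
| t test, month 12 | 1.00 | 252 | 48% | 56% |

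Only the first row gives 117. The t test on the 1-year value, which is how the endpoint is worded, has 48% power. Adjusting for baseline at month 12 brings this only to 55%. Most of the gap to 80% comes from averaging four visits.

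**3. Sensitivity to the endpoint scale.** The SD of 2 is given for HbA1c, while the endpoint subtracts a target. The documents give no SD for the target. If one assumes a target SD of 0.3 to 0.7 and a correlation of 0 to 0.4 with 1-year HbA1c, the month-12 t test has 44% to 55% power at 117 per arm and needs 212 to 282 per arm.

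**4. Correlation between the two test statistics.** The t test uses the month-12 value. The adjusted analysis uses its outcome minus 0.4 × baseline.

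- Visit-averaged contrast: covariance = σ²(0.625 − 0.16) = 0.465σ², so the correlation is 0.465/√(1 × 0.465) = √0.465 = 0.68.
- Month-12 contrast: covariance = σ²(1 − 0.16) = 0.84σ², so the correlation is √0.84 = 0.92.

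**5. Chance that at least one |Z| exceeds 1.96 under the null (bivariate normal).** It is 8.4% for the visit-averaged contrast and 6.9% for month 12. Independent tests would give 1 − 0.95² = 9.75%, the ceiling.

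**6. Disagreement at δ = 0.5 and 117 per arm.** The expected Z is 0.5/(2 × √(2 × factor/117)): 1.91 for the t test, 2.80 for the visit-averaged model and 2.09 for the month-12 model.

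| Model contrast | Only model significant | Only t test significant | Disagree |
|---|---|---|---|
| Average over visits | 34.0% | 2.0% | 36% |
| Month 12 | 10.6% | 3.6% | 14% |

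These figures use baseline adjustment alone. They leave out the model's other covariates and missing data.

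**The case against.** The strongest reply is that the article already points to the mixed model. The 117 per arm fits a baseline-adjusted, repeated-measures analysis and nothing else tried here. A crude result followed by an adjusted one is a common reporting order. The article is condensed, and Data collection method refers to a statistical analysis plan that is not shown and might name the decisive test. This makes the remedy mainly a clarification. It does not remove the point, because the article is not silent: it fixes two between-arm comparisons, puts the unsized one first, and reserves the sensitivity label for LOCF.

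Four stronger readings are tempting, and the documents do not support them.

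- *The trial runs at an inflated error rate.* The analysis section gives no significance level for either test and does not say that either result may be claimed. The 6.9% to 8.4% is conditional on that.
- *The t test drops patients without a 12-month value and so breaks the ITT commitment.* Analysis population says "Efficacy will be analyzed on an intent-to-treat (ITT) basis", and LOCF is planned as a sensitivity analysis. How the t test treats missing values is not stated.
- *The t test is invalid, or its main cost is ignoring baseline.* An unadjusted t test is valid in a randomized trial, and ignoring the stratification does not inflate its type I error. Most of its power loss comes from using one visit, which follows from the endpoint definition.
- *The secondary outcomes need the same repair.* They follow a similar two-step sequence, but the 5% in the sample-size section belongs to the primary comparison, and no confirmatory claim is stated for them.

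**Conclusion.** The point holds in a limited form. The article prescribes two tests of the primary outcome, names neither as decisive, and lists first a test that the sample size does not support: about 48% power at 117 per arm and 56% if all 141 are evaluable, against a planned 80%. If either success could be claimed, the type I error would be about 7% to 8%. At the design effect the two tests would disagree in about 14% of trials (month-12 contrast) or 36% (visit-averaged contrast). In most of those the stronger model alone succeeds; the t test alone succeeds in 2% to 4% of all trials.

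These sizes rest on the protocol's own SD and correlations carrying over to HbA1c minus target. The missing decision rule does not depend on them.

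Naming the mixed model does not settle everything, because a month-12 contrast was not what the sample size was built on either.

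**What to change.** 1. Name the baseline-adjusted mixed model as the single decisive primary analysis, at two-sided 5%.
2. Relabel the Student's t test as an unadjusted supportive description that carries no claim.
3. State the model's treatment contrast and make it agree with the Sample size section, in one of two ways:
   - *Average over months 3 to 12.* 117 per arm then gives 80% power, and the endpoint wording in Outcomes and in Primary outcome analysis must be aligned with it.
   - *Month 12.* The endpoint wording stands, but the power must be restated: by simple ANCOVA about 55% at 117 and 63% at 141 per arm, with 211 per arm needed for 80%.

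Adding the randomization stratum to the model is optional, since baseline HbA1c is already a covariate.

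Steps 1 and 2 take a sentence in the protocol or SAP and need no new data. Step 3 costs more: it means either a documented change of endpoint wording or an openly lower power. It should be settled before outcome data are compared between arms.

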## Background

According to the World Health Organization (WHO), 422 million people suffer from diabetes world-wide. This qualifies as a genuine pandemic since progression is considerable. Thus the WHO is forecasting that 622 million people will be suffering from diabetes between now and 2040 [1]. Over 90% of these people present type 2 diabetes. The severity of diabetes, from both a human and economic perspective, is the onset of chronic complications associated with the disease. To avoid or delay their onset as much as possible, patients with diabetes must improve the way in which they manage their blood glucose levels. Type 2 diabetes patients can be treated in different ways, depending on disease advance, ranging from a change in lifestyle alone, oral treatments or multiple insulin injections, or a combination of all options. The French Health Authorities (HAS) continue to advocate the following first-line therapy: a change in lifestyle with a change in diet and regular physical exercise for improved blood glucose management together with weight loss, if applicable [2, 3]. These measures must be maintained long-term even when combined with medication. Numerous studies have shown that a change in lifestyle can improve patients’ blood glucose levels but long-term results are difficult to maintain [4–6]. Thanks to technological innovation, health-related devices can now be used to monitor patients remotely in their own homes and play a greater role in daily routines by helping patients to improve their lifestyle and adjust their treatment [7–12].

We want to compare telemonitoring management incorporating therapeutic education tools for type 2 diabetes with standard monitoring. We believe that this telemonitoring management approach will improve patients’ blood glucose levels, lifestyle and quality of life whilst rationalizing recourse to consultations, thus helping to reduce the incidence of complications and long-term costs.

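### LOCF, the only missing-data sensitivity analysis named for 1-year HbA1c, does not test the mixed model's missing-at-random assumption, and its bias can go either way

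*Protocol article*

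**What the plan says.** The Outcomes section defines the endpoint: "The primary endpoint is the difference between HbA1c level after 1 year of follow-up and the targeted HbA1c level defined at baseline". It also gives the schedule: "HbA1c levels will be measured at baseline, 3, 6, 9 and 12 months of follow-up". The Primary outcome analysis section compares the arms "firstly using bivariate analysis (Student’s T test), and secondly using mixed model analysis for repeated measures", with the mixed model adjusted for baseline HbA1c and other baseline variables. On incomplete data it has one sentence, which says that to deal with them "a sensitivity analysis using the last observation carried forward (LOCF) technique will be applied".

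No other missing-data analysis is named for efficacy. The sensitivity analysis under Methods for medical-economic analysis concerns the economic model. The Analysis population section sets the frame: "Efficacy will be analyzed on an intent-to-treat (ITT) basis followed by a per protocol (PP) analysis, if required".

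**The concern.** A mixed model fitted to all observed visits gives valid estimates if data are missing at random, that is, if loss depends only on what has been recorded. The useful sensitivity question is how the result changes when that assumption fails. LOCF does not ask it. It puts another single assumption in its place, that HbA1c stays at its last value until month 12, and adds no uncertainty for the values it fills in. If LOCF and the mixed model agree, little is learned about robustness. If they disagree, the reader cannot tell which assumption is at fault.

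The frozen-value assumption also sits uneasily with the protocol's own rationale. The Background says that "a change in lifestyle can improve patients’ blood glucose levels but long-term results are difficult to maintain". If an early fall in HbA1c fades and some patients leave while it is still visible, LOCF carries the early fall to month 12 and reports it as a 1-year effect. At stake is whether the one robustness check on the primary result can be relied on.

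**Working it through.** **Inputs from the protocol article.** HbA1c at baseline, 3, 6, 9 and 12 months (Outcomes). SD 2 points, correlation 0.4 between pre- and post-randomization values, correlation 0.5 among post-randomization values, difference 0.5, power 80%, two-sided 5%, 117 per arm raised to 141 (Sample size).

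**Step 1: reproduce the stated sample size.** With one baseline and four follow-up values, the variance factor is (1 + 3 × 0.5)/4 − 0.4² = 0.625 − 0.16 = 0.465. Then n = 2 × (1.960 + 0.842)² × 2² × 0.465 / 0.5² = 116.8, so 117 per arm, as stated. 117 × 1.2 = 140.4, so 141. The total rises from 234 to 282, and the loss covered is 48/282 = 17%.

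**Step 2: expected LOCF difference.** In each arm, let w(k) be the share of patients whose last value is at visit k, and m(k) the mean at that visit. The LOCF mean is the sum of w(k) × m(k), and the LOCF difference is telemonitoring minus control. The baseline target is fixed for each patient, so freezing HbA1c freezes the endpoint too. The expected difference does not depend on the SD.

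**Step 3: scenarios.** Effect paths, loss by arm and timing of loss are assumed. Negative values favour telemonitoring. Evenly spread means that last values fall equally at baseline, 3, 6 and 9 months.

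| Assumed course | Loss, telemonitoring / control | True 12-month difference | LOCF difference |
|---|---|---|---|
| −0.5 at month 3, waning linearly to 0; evenly spread | 17% / 17% | 0 | −0.04 |
| Same | 20% / 20% | 0 | −0.05 |
| Same | 30% / 10% | 0 | −0.075 |
| Same waning, all losses just after month 3 | 17% / 17% | 0 | −0.085 |
| Same | 20% / 20% | 0 | −0.10 |
| No effect at any visit | equal | 0 | 0 |
| No effect, both arms improve linearly by 0.5; evenly spread | 30% / 10% | 0 | +0.06 |
| Same | 10% / 30% | 0 | −0.06 |
| Sustained −0.5; evenly spread | 20% / 20% | −0.5 | −0.475 |

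Worked examples:
- Waning, evenly spread: the mean carried difference is (0 − 0.5 − 0.333 − 0.167)/4 = −0.25; × 0.20 = −0.05.
- Waning, all lost after month 3: −0.5 × 0.20 = −0.10.
- Sustained: 0.8 × (−0.5) + 0.2 × (0 − 0.5 − 0.5 − 0.5)/4 = −0.40 − 0.075 = −0.475. With no loss before month 3 it would be −0.5, without bias.

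**Step 4: size.** At 17% to 20% loss per arm with a waning effect, the false benefit runs from 0.04 to 0.10 points; 0.04/0.5 = 8% and 0.10/0.5 = 20%. At SD 2 and 141 per arm, the baseline-adjusted standard error of a 12-month difference is about √(2 × 4 × (1 − 0.4²)/141) = 0.22, so the bias is at most about half a standard error.

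**Step 5: simulation.** 4,000 runs per scenario, 141 per arm, the plan's SD and correlations, analysis adjusted for baseline, losses evenly spread and unrelated to outcome. In four settings with a true 12-month difference of 0 but a waning effect or unequal loss, LOCF rejected in 5.6% to 6.1% of runs. With no effect and equal loss it rejected in 4.8%. Monte Carlo error is about √(0.05 × 0.95/4000) = 0.3 percentage points, so the excess is small.

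**The case against.** The strongest reply is that LOCF is labelled a sensitivity analysis. A mixed model fitted to the observed visits already uses incomplete patients under missing at random, so the primary estimate need not depend on LOCF. That stands. A reader might infer that the main result is biased, and the article does not support this. It does leave some doubt by introducing LOCF as the means of managing missing data without saying which data the t test and the mixed model use.

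A reader might also infer that LOCF will favour telemonitoring. The text does not support that either:

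- The Background sentence concerns long-term maintenance of lifestyle change. It does not say that an effect vanishes within the 12 months in which the device is still in use.
- Only the intervention arm carries the burden of the device, but stopping the device is not the same as a missing HbA1c. Under Data collection method, research associates telephone patients quarterly for two years for the HbA1c result, with no restriction to device users. The project team also contacts intervention patients who have not connected for more than 15 days. Nothing shows which arm would lose more patients.
- The last four rows of the table show zero bias, or bias in either direction. The +0.06 against telemonitoring arises with the larger loss in the telemonitoring arm.

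Nor does the plan forecast 20% loss. It enlarges the cohort by 20% with the stated purpose "To avoid any loss of power due to patients lost to follow-up", and that covers 17%.

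Finally, a separate statistical analysis plan may add further analyses. That does not remove the point, because the article itself fixes LOCF as the check.

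**Conclusion.** The point holds as a criticism of the chosen check. LOCF does not probe departures from missing at random, so agreement with the mixed model would be weak evidence of robustness. This conclusion needs none of the assumed scenarios.

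The size does rest on them. With a 0.5-point effect waning to zero by month 12 and 17% to 20% loss in each arm, the false 12-month benefit is about 0.04 to 0.10 points. With a sustained effect and some loss before month 3, the LOCF estimate is conservative. The effect on false-positive findings was small in simulation. The change is worth making because a better analysis is available at little cost and a bias of unknown direction is a poor basis for the only check. It is not grounds for doubting the main mixed-model estimate.

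**What to change.** In the Primary outcome analysis section:

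1. State that the mixed model, fitted to all observed 3-, 6-, 9- and 12-month HbA1c values, is the main handling of missing data. Include values from patients who stopped using the device, and say that no LOCF-filled values enter it.
2. Replace LOCF with multiple imputation under missing-not-at-random assumptions, applied only to patients whose 12-month HbA1c is actually missing. A delta-adjusted tipping-point analysis, with the shift varied separately by arm, would report how far the missing values must differ from their missing-at-random prediction before the conclusion changes. Control-based imputation is an option alongside it.
3. Fix the range of shifts before the database is frozen.

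The cost is a little more programming. No new data, visits or patients are needed, and the sample size does not change.
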